### Study procedures

Participants are being drawn from the greater central Ohio area. Recruitment for the study started in August 2018 and is currently ongoing. We are implementing a multi-medium recruitment strategy, advertising for the study using both printed and online communications, in-person recruitment, community outreach, and other opportunities aimed at our targeted demographic. Table 1 provides a list of our primary recruitment sources for the study. Participants interested in the study will either complete a phone screen or an online survey that is designed to collect basic demographic information, current medications, and history of physical as well as psychological health. Participants who meet basic inclusionary criteria are then invited to the Clinical Neuroscience Laboratory at The Ohio State University to complete an in-person screening session. Those meeting the study criteria as described above are invited for additional behavioral and imaging-based assessments. Table 2 lists the measures administered at pre-training, post-training, and at 6-month and 12-month follow-up sessions. Participants are also given a Qualtrics link with the following survey measures at baseline, pre-training, post-training, and the two follow-up sessions: the Mindful Attention Awareness Scale [53], the Difficulties in Emotion Regulation Scale [54], the Perceived Stress Scale [55], the World Health Organization Quality of Life – BREF [56], the Beck Anxiety Inventory [57], the Five Facet Mindfulness Questionnaire [58], the Coronavirus Anxiety Scale [59], Psychological Stress Associated with the COVID-19 Crisis [60], and the Everyday Discrimination Scale [61].

**Table 1 Tab1:** List of primary recruitment sources being employed for the study

Category	Recruitment Strategy
**Printed Materials**	Flyers were displayed in recreational centers, community centers, libraries, cafes, barber shops, and churches throughout the central Ohio area
	Advertisements were displayed on Campus Area Bus Service buses at The Ohio State University
	Post cards were distributed to households in the central Ohio area
**Online Recruitment**	Research Match (an online recruitment tool with a database of participants.)
	Study Search (a database of active studies at The Ohio State University)
	Media advertisements (Facebook, Columbus Dispatch, Ohio State University’s OnCampus newspapers)
**Radio Advertisement**	Radio Stations aired an advertisement for the study (106.7 The Beat)
**Snowball Recruitment**	To facilitate oversampling of individuals from historically marginalized populations, a referral recruitment strategy was implemented. For this, enrolled participants could refer potentially eligible friends or family members to the study to receive an additional $5 per referral, up to a maximum of $35, when the individual contacted the study’s research team

**Table 2 Tab2:** Measures being administered across study visits for the HealthyAgers Trial

Procedure	Visit 1 Screening	Visit 2 Pre-intervention	Visit 3 Post-intervention	Visit 4 6-month Follow-up	Visit 5 12-month Follow-up
Written Informed Consent	X				
Eligibility Criteria Assessment	X				
Cognitive Status Battery					
MCI	X				
MoCA^a^	X				
Questionnaires		X	X	X	X
Behavioral					
Go/No-Go	X^b^	X^b^	X	X	X
Conner’s CPT-3	X^b^	X^b^	X	X	X
NIHTB Cognition		X	X	X	X
ERC		X	X	X	X
NAB Driving Scenes		X	X	X	X
Neuroimaging^c^		X	X		X
Blood Draw		X	X		X

*Conner’s CPT* Conner’s Continuous Performance Test-3, *ERC* Emotion Regulation Choice task, *MCI* Mild Cognitive Impairment assessment battery, *MoCA* Montreal Cognitive Assessment, *NAB Driving Scenes* Neuropsychological Assessment Battery Driving Scenes test, *NIHTB Cognition* National Institute of Health Toolbox Cognition Battery

^a^ MoCA is only administered if an administration error occurs during the MCI assessment battery

^b^ Administration of GNG and Conner’s CPT are split between the Screening and Pre-intervention visits and are counterbalanced across participants

^c^ Participants with contraindications for the MR environment complete a non-MRI assessment

### Primary outcome

The primary outcomes for this study are changes in measures of attentional control and mind-wandering during tasks of sustained attention. To quantify both attentional control and mind-wandering the following measures are being administered:

#### Go/No-Go

In this task, participants are presented with one of two visual stimuli (“X” and “M”, or “Z” and “/”) for 750 ms followed by an inter-trial-interval of 750 ms. They are asked to press the corresponding key on frequent Go trials and to withhold responses on the less frequent (occurring 10% of the time) No-Go trials signaled by an auditory tone. Participants complete six blocks of this task with each block containing 54 Go trials, six No-Go trials, and three mind-wandering probes. The quasi-randomly presented mind-wandering probes ask participants to categorize their immediately preceding thought as: 1) “On-task”, 2) “thinking about performance on the task”, or 3) “thinking about personal worries, day-dreaming, fantasizing or just lost in thought.” The primary outcome variable for attentional control will be the signal detection sensitivity index (d_L_). The d_L_ provides a measure of task performance and will be calculated using the formula for logistic distributions: d_L_ = ln{[H(1-FA)]/[(1-H)FA]}, where H refers to hit rates for go trials and FA refers to false alarms on no-go trials. The primary outcome variable for mind-wandering will be the proportion of off-task probes endorsed by the participant. In addition, we will compute response-time variability—the trial-by-trial fluctuation in reaction time—as an indirect marker of mind-wandering.

#### Conner’s continuous performance test

In this task, participants are presented with a series of letters displayed one at a time on the screen and are instructed to press the space bar as quickly as possible for all letters (target), except for the letter ‘X’ (non-target). Participants are instructed to withhold their responses during ‘X’ letter (non-target) trials. Participants complete six blocks of 60 trials each in which letters are presented for 250 ms and inter-stimulus intervals are 1, 2, or 4 s in duration. Participants’ ability to differentiate between non-targets and targets is reflected by detectability (d’) scores and will be the primary outcome assessing attentional control. Participant d’ scores are reverse-scored such that higher *T*-scores reflect worse performance (i.e., poorer discrimination between targets and non-targets). Response time variability (RT variability), an index of mind-wandering for this task, is a measure of response speed consistency and will be calculated as the standard deviation of each participant’s response time (ms) on correct trials. Higher RT variability scores is indicative of varying attentional states and will be employed as an indirect index of mind-wandering in this task.

The efficacy of the intervention for sustained attention will be determined by improved performance on both measures. Similarly, we will conclude that mindfulness training causally impacts mind-wandering if there are reductions in both self-reported mind-wandering (i.e., on embedded probes) and in response time variability.

### Secondary outcomes

Secondary outcomes in this study include neuroimaging assessments, measures of fluid cognition, everyday cognition, and emotion regulation strategy use, and systemic markers of inflammation.

#### Neuroimaging assessment

Functional MRI (fMRI) and structural MRI data will be collected at pre-training, post-training, and at 12-month follow-up. The primary dependent variable from the neuroimaging data is the network strength in a connectome-based predictive model of sustained attention (saCPM; [62]). Figure 2 presents the functional neuroanatomy of the high attention model (includes functional connections that positively predict attentional control) and the low attention model (includes functional connections that negatively predict attentional control). The saCPM model, combining the functional connections of the high and low attention models, will be employed in the current study. Network strength in this whole-brain, functional connectivity-based model of attentional control predicts performance on variegated tasks of attentional control [63–65], generalizes to predict performance across young adults [66], older adults [65], and individuals with attention-deficit hyperactivity disorder [62], and, critically, shows responsiveness to change following methylphenidate treatment for attention-deficit hyperactivity disorder [63]. Participants will perform the gradual-onset continuous performance task (gradCPT; [62, 67, 68]) while in the scanner. In this task, participants view circular images of city and mountain scenes. Participants are asked to respond to the frequently occurring city scenes (~ 90% of images) and to withhold responses to mountain scenes. Participants will complete two separate runs with each run lasting 13 min and 44 s. Neuroimaging data will be checked for quality control and preprocessed using our lab’s established pipelines [69]. The preprocessed 4D data for each participant will be parcellated into 268 contiguous and functionally defined regions using a parcellation scheme covering the cortex, subcortex, and cerebellum [70]. The connections between each pair of these nodes, defined as edges, will be computed by correlating the time-course of activity between the nodes. This will result in a 268X268 functional connectivity matrix with cells of the matrix representing the magnitude of these edges or correlations. Using the network mask of the saCPM neuromarker [63], which has been validated in our prior work with older adults [71], we will compute the network strength of the marker for each participant at pre-training, post-training, and at 12-month follow-up.

**Fig. 2 Fig2:**
[figure not shown]
Functional neuroanatomy of the sustained attention connectome-based predictive model (saCPM). **A** Presents the involvement of the ten canonical networks in the high attention model with edges representing functional connections that positively predict attentional control. Ribbons in the ring plot visualization are proportional to the representation of each network in the saCPM model. The matrix presented on the bottom shows the relative contribution of each network to the saCPM model adjusted using the formula described in Greene et al., 2019. Panel **B** highlights the network localization of the low attentonl model with edges representing functional connections that negatively predict attentional control. The matrix on the bottom shows the relative contribution of each network in the saCPM model. Chord diagrams were generated using the software Flourish (v7.0.0, https://app.flourish.studio)

#### NIH cognitive toolbox

The cognition battery of the NIH Toolbox was designed as part of the NIH Blueprint for Neuroscience Research [72] to assess cognitive functioning across multiple domains in a standardized format. The battery is designed for use with participants between the ages of 3–85 with alternate forms available for longitudinal assessments. All tasks will be completed using fifth generation iPads with set-up and administration standardized across all participants. We will employ the fully corrected fluid cognition T-scores that norm for age, gender, education, and race/ethnicity for the following five tasks: Pattern Comparison Processing Speed, List Sort Working Memory, Picture Sequence Memory, Dimensional Change Card Sort, and Flanker Inhibitory Control and Attention. Please see Supplementary Materials for a detailed description of each of these tasks.

#### Neuropsychological Assessment Battery (NAB) driving scenes

Driving is an important functional domain that plays a critical role in the independence of older adults. To assess the impact of the intervention on functional ability, participants are being administered the Driving Scenes subtest of the NAB as a proxy measure of everyday functional ability. This measure has been shown to serve as a valid proxy for real-world driving abilities [73], it can identify at-risk drivers [74], and it is associated with global cognitive impairment in older adults with and without cognitive impairment [75]. Participants are presented with one driving scene for 30 s. This is followed by the presentation of a new scene for 60 and up to 120 s. Participants are asked to identify elements of the new scene that may be new, diferrent, or missing compared to the first scene. The main dependent variable from this task is the total number of correctly identified elements as adjusted for age, sex, and education [76].

#### Emotion regulation task

Participants complete an adapted version of the Emotion Regulation Choice Task originally developed by Sheppes and colleagues [77]. Participants are shown a series of 24 negatively valenced images and are instructed to regulate their emotions to each image using one of two emotion regulation strategies, namely acceptance or suppression. Twelve of the trials consist of low-intensity images and the remaining 12 trials consist of high-intensity images. All images were taken from the International Affective Picture System [78]. Prior to completing the task, participants undergo a brief training in which they read about each emotion regulation strategy and are asked to verbalize to the experimenter how they are using these strategies during the six practice trials. The order for which emotion regulation strategy is learned first will be counterbalanced across participants. Broadly, acceptance is defined as allowing one’s feelings to come and go without trying to control or avoid them, and suppression is defined as pushing one’s feelings down or out of one’s mind. Following the practice trials, participants proceed to the 24 task trials. Overall acceptance use will be calculated as the percentage of total trials (24 trials) in which the participant chooses to use acceptance to regulate their emotions. Acceptance use will be quantified as the percentage of low- and high-intensity images (12 trials each), respectively, in which the participant chooses to use acceptance. Scores can range between 0 and 100 percent, and higher scores reflect a greater preference for acceptance.

#### Systemic markers of inflammation

Blood samples will be collected between 8:00 am-10:00 am by a trained phlebotomist at three timepoints: pre-training, post-training, and at the 12-month follow-up session. Following standardized protocols, and implementing same control for each participant at all time points, the frozen samples for each participant will be assayed for the inflammatory markers at the same time. Various peripheral inflammatory markers exist which may be investigated for their association with cognition; however, there is strong support for C-reactive protein, interleukin-6, and tumour necrosis factor alpha to be consistently associated with cognitive outcomes in older adults [79, 80]. Additionally, these inflammatory markers appear to be reduced following mindfulness meditation interventions in a dose–response relationship [81–83]—an effect with several biologically plausible mechanisms [84–86]. This relationship appears particularly robust in older adults [87]. Although some previous studies have examined composite scores from multiple inflammatory markers, these composites are not standardized across studies and biomarkers are implicated in unique physiological processes [88–90]. Therefore, we will examine peripheral inflammation via these three markers independently.

### Randomization

Eligible and consenting participants will be randomized after completing baseline assessments to one of two groups: MBSR or LifeEd. A random permuted-block design (blocks of size 2 and 4) will be used, and the randomization with an allocation ration of 1:1 will be stratified by sex assigned at birth (male, female), cognitive status (cognitively normal, MCI), and MRI eligibility (eligible, not eligible) to ensure balance across these important factors. The biostatistician on the team, [name], prepared and maintains the randomization sequence for the eight strata. The project coordinator has been given concealed envelopes and only after a participant completes all pre-assessment sessions and is deemed eligible for the study does the project coordinator open the envelope from the respective stratum and assign the participant to either the MBSR or the LifeEd group. The project coordinator, the study facilitators and supervisors, and the study biostatistician will be the only members of the team who will be unblinded to group assignment. All personnel conducting assessments, behavioral or neuroimaging, will remain blind to group assignment.

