### Participant eligibility

Participants will only be included in the study if they satisfy the following criteria: aged between 65–85 years, corrected (far) visual acuity of 20/40 or better, have adequate hearing for assessment purposes, and have self-reported proficiency in spoken English and in reading comprehension. Additionally, we will only include participants if they are able to attend the majority of eight-week sessions and attend all assessment sessions, have a self-reported interest in engaging in mind–body interventions, can commit to a 30-min homework practice five times per week, and have the ability to engage in light stretching and toning exercises.

Additionally, participants will only be included in the study if they are classified as cognitively normal or having mild cognitive impairment (MCI) based on a battery of neuropsychological measures employed to screen individuals with dementia [36, 37]. The screening battery includes the following measures and seven dependent variables used for exclusionary determinations: 1) total recall and 2) delayed recall from the Hopkins Verbal Learning Test—Revised ([38], 3) total score on the Block Design and 4) total score on Digit Span subtests from the Wechsler Adult Intelligence Scale-IV [39], 5) total score on the FAS Verbal Fluency Task [40], 6) total score on the Boston Naming Test [41], and 7) perseverative errors on the computerized version of the Wisconsin Card Sort Test [42]. The WAIS-IV subtests are completed between the immediate and delayed recall tasks of the Hopkins Verbal Learning Test. Descriptions of each of these measures and details on their scoring and norms are provided in Supplementary Materials. Participants will be excluded from the study due to having impairment levels consistent with dementia based on one of the following criteria: 1) if at least one normed score in both the memory and non-memory domains is < -2 *S.D.*s below the mean (i.e., T < 30), 2) if the average of their normed scores on all seven neuropsychological measures is < -2 *S.D.s* (i.e., average T < 30), or 3) if the participant reports less than intact function on all items of the Lawton Instrumental Activities of Daily Living [43] (< 8/8 points).

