#### Assessing and maximizing adherence

Our lab has successfully conducted two RCTs on mindfulness training, and for both those studies, we have had adherence rates of ~ 80% (Whitmoyer et al., 2020; Schirda et al., 2020). In the current study, we will implement a number of strategies that have been successful in the past to promote adherence to the intervention as well as the assessment sessions. First, as both groups in the study will engage in training that promotes and discusses healthy aging, advertising the study as a trial on mind–body interventions for healthy aging will help recruit individuals with a genuine interest in making these changes. Second, detailing the study requirements in the recruitment materials, particularly the 30 min of daily practice for eight weeks, appears to have a positive influence on adherence to homework practices and retention rates. All our advertisement materials detail this time commitment on behalf of the participants. Third, once participants are enrolled in the study, weekly attendance at the online sessions is being monitored by course facilitators and communicated to the study coordinator. For every missed session, the study coordinator connects with the participant, and either schedules them for an individual appointment with the course facilitator or sends them a summary from the missed session. For participants who wish to not continue with the intervention, every attempt will be made to complete the assessment sessions.

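### An unblinded coordinator holds the stratum envelopes with blocks of only 2 and 4, so about 71-72% of upcoming assignments can be guessed from stratum history, leaving room for selection through the timing or order of allocation

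*Protocol article*

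**What the plan says.** All of the allocation procedure is in the Randomization section of the protocol article.

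- **Sequence.** "A random permuted-block design (blocks of size 2 and 4) will be used", with 1:1 allocation, stratified by sex, cognitive status and MRI eligibility. The biostatistician "prepared and maintains the randomization sequence for the eight strata".
- **Custody.** "The project coordinator has been given concealed envelopes and only after a participant completes all pre-assessment sessions and is deemed eligible" is the envelope used; then "does the project coordinator open the envelope from the respective stratum and assign the participant to either the MBSR or the LifeEd group".
- **Blinding.** The project coordinator is on the short list of people who know group assignment. Staff who carry out assessments stay blind.

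Three other places bear on the point. Table 2 (Study procedures) puts the assessment of eligibility criteria at the screening visit. The Participant eligibility section contains at least one forward-looking criterion: "we will only include participants if they are able to attend the majority of eight-week sessions". The Discussion says that participants are recruited six to eight at a time, to form a class.

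**The concern.** Concealment requires that whoever controls the moment of allocation cannot foresee the result. Here the same person holds the envelopes, opens them and knows the earlier assignments. A participant's sex, cognitive status and MRI eligibility are settled by the end of pre-assessment, so the relevant stratum, and its history, are known before the envelope is opened. With blocks of 2 and 4 that history is informative.

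If the likely next arm is known, a participant who seems keen or reliable could be allocated now or a little later. Such selection would bring differences in motivation into the groups, and motivation plausibly bears on attendance, homework and effort on the attention tasks. Blinded assessors protect against biased measurement, not against this. The mixed model can adjust for measured covariates that differ at baseline, but not for unmeasured motivation.

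**Working it through.** The article gives no predictability figure, so there is nothing of its own to reproduce.

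**Inputs.** Block sizes 2 and 4, ratio 1:1 and eight strata (Randomization). Total sample 150 (Study design), or at least 130 (Sample size). Average stratum length is 150/8 = 18.75 or 130/8 = 16.25 if participants spread evenly. The mix of block sizes is not stated; equal probability is assumed and then varied.

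**Guessing rule.** Guess the arm that is behind in the stratum, and toss a coin when the arms are level. This needs no knowledge of the block sizes.

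*Block of 2.* The first guess is worth 1/2 and the second is always right: 1.5 of 2 = 75.0%.

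*Block of 4.* By symmetry, take the three orders that start with A:
- AABB: 0.5 + 0 + 1 + 1 = 2.5
- ABAB: 0.5 + 1 + 0.5 + 1 = 3
- ABBA: 0.5 + 1 + 0.5 + 1 = 3

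The mean is 8.5/3 = 17/6 = 2.83 of 4 = 70.8%.

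*Mix.* Expected correct guesses divided by expected length, with p the share of blocks that have size 2:

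[1.5p + (17/6)(1 − p)] / [2p + 4(1 − p)]

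| p | Correct |
|---|---|
| 0 | 70.8% |
| 0.25 | 71.4% |
| 0.5 | 72.2% |
| 0.75 | 73.3% |
| 1 | 75.0% |

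**Finite strata.** A simulated guesser who knows that the sizes are 2 and 4, equally likely, but not their order, was right this often:

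| Stratum length | Correct | Known with certainty |
|---|---|---|
| 3 | 63.9% | 5.5% |
| 8 | 71.4% | 9.2% |
| 16 | 71.7% | 10.3% |
| 19 | 70.9% | 10.4% |
| 150 | 72.2% | 11.0% |

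**Check on certainty.** A lead of two can arise only inside a block of 4 that starts with two alike, and the next two assignments are then fixed. This happens in 1/3 of such blocks and gives 2 × 1/3 = 2/3 of a certain assignment per block of 4. One block of each size makes 6 assignments, so the long-run share is (2/3)/6 = 11.1%, in line with the simulation.

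**In participants.** For 150 randomized, 0.71 × 150 ≈ 107 correct guesses, against 75 by chance, and 0.10 × 150 = 15 certain.

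**Larger blocks.** Sizes 4, 6 and 8 in equal shares give (2.833 + 4.100 + 5.329)/18 = 68.1% by the same rule. Simulation gives 65.8% to 67.6% at stratum lengths of 10 to 40, with about 2.5% certain.

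**The case against.** The best defense is that the article leaves little discretion at the envelope. Table 2 puts eligibility at screening, only those who meet the criteria go on to baseline, blinded staff run those sessions, and the envelope comes last. Many criteria are normed scores, cut-offs, diagnoses or medication classes. Queue rules and logs are operational details that an article may leave to the full protocol. Small blocks also protect balance in strata that average fewer than 20 people.

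Much of this stands, and it rules out several stronger readings that a reader might infer:

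- *That the coordinator decides eligibility or sets the order of opening.* The article says neither.
- *That the coordinator's regular contact with participants feeds the selection.* The contact described under Assessing and maximizing adherence ("For every missed session, the study coordinator connects with the participant") follows missed intervention sessions, so it comes after randomization. That section also says study coordinator, where Randomization says project coordinator.
- *That a judgement of genuine interest is an entry criterion.* That phrase concerns advertising; the criterion itself is self-reported interest.
- *That larger blocks are the cure.* They leave about 66-68% guessable and loosen balance in small strata.

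What the defense does not remove is the stated arrangement: an unblinded holder of the envelopes, and short blocks. The Randomization section itself puts the eligibility decision directly before the envelope ("is deemed eligible for the study does the project coordinator open the envelope from the respective stratum") and names no decider. It describes allocation one participant at a time, and recruitment by class means that several people may be waiting together. How often two of them share a stratum is not stated.

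**Conclusion.** The point holds as a weakness in concealment that follows from the stated procedure, and it should be corrected for the participants still to be randomized. Predictability is about 71-72% against 50% by chance, with about 10% of assignments certain, if the sizes are equally likely and someone follows the stratum histories. The range of 70.8% to 75.0% covers any mix of the two sizes in long sequences; a stratum of 3 gives about 64%.

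These figures measure how foreseeable the assignments are, not how large a bias is. A reader might infer that the groups are already distorted; nothing in the article shows that, and no effect on an outcome can be derived from it.

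**What to change.** For participants not yet randomized:

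1. Record final eligibility, stratum and queue position, defined as the order of completing baseline, before any assignment is requested. The blinded assessment staff are the natural people to make this entry.
2. Have the biostatistician release the next assignment in the stratum by participant ID, strictly in queue order. The coordinator returns the unused envelopes and learns each assignment only on release.

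This does not make the sequence harder to guess; it takes away the means of acting on a guess. It needs no new staff, because the biostatistician already maintains the sequence and is already unblinded. Assignments already made are unaffected. The cost is a short wait for each release.

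Regenerating the unused part of the lists with larger mixed blocks is optional. It would cut certain assignments from about 10% to about 2.5%, but correct guesses only to about 66-68%, at the price of looser balance in small strata. It is not part of the required change.
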